### Recruitment {15}

Participants will be invited to participate in the study through social media sites (e.g., Facebook and Instagram), leaflets, paper and digital flyers, websites, and online news sources from the University of Hartford. After selecting the participants, a subjective interview will be conducted to assess the sample eligibility.

## Assignment of interventions: allocation

### Sequence generation {16a}

The order of active TENS, placebo TENS and no TENS will be randomized via the website (randomization.com).

### Concealment mechanism {16b}

Concealment of the treatment order will be achieved using sequential numbering in sealed opaque envelopes, which will be stored in a secure cabinet and only be opened before the first session by the researcher responsible for the application of the TENS treatments.

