**Methods/design:**

This study will be a randomized crossover trial. The participants for this study will be recruited from various places, including the University of Hartford, physical therapy clinics, and local businesses in the Hartford area, as well as online websites geared towards clinical trial recruitment. A total of 34 participants will receive all three treatments: active TENS, placebo TENS, and no treatment control. The treatment order will be randomized using a website-based randomization tool. For active TENS, a modulating frequency of 2–125 Hz will be applied with a variable pulse duration and maximal tolerable intensity for 30 min. The TENS will be left on for post-treatment testing to assess the effects during its maximally effective period for a total of 50 to 60 min. Furthermore, the intensity may be turned down if muscle twitching is present to ensure blinding of the evaluator. For placebo TENS, the unit will deliver current for 45 s, ramping to 0 in the last 15 s. The primary outcome will be pain intensity at rest and with movement, determined using the numerical pain rating scale. The secondary outcomes will be pressure pain threshold, heat pain threshold, temporal summation of pain, conditioned pain modulation, sit-to-stand test, and repeated trunk flexion. The assessments will be performed immediately before and after treatment. Statistical analysis of the data obtained will consider a significance level of *p* < 0.05.

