#### Active TENS

An EMPI Select TENS unit will be used to deliver the active TENS intervention. A modulating frequency TENS (2–125 Hz) will be applied with a variable pulse duration, waveform of an asymmetrical biphasic square wave, and maximal tolerable intensity [11, 15]. With this specific unit, current intensity ranges from 0.5 to 60.0 mA and the participants will be educated prior to intervention on what they will feel. TENS will be placed for 30 min after baseline testing and then remain on for the post-assessment tests to assess the effects during its maximally effective period [10] for a total of 50 to 60 min. Every 5 min, the subject will be asked if the intensity can be increased, decreased or remain the same to maintain the same level of intensity. The intensity may be turned down if muscle twitching is present during post-assessment testing maintain blinding of the evaluator.

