### Participant timeline {13}

Participants will be asked to complete a self-administered questionnaire that collects demographic information such as age, sex, marital status, education level, ethnicity, race, income, and history of surgeries. Weight will be measured using a calibrated electronic scale, height will be measured using a stadiometer, and the body mass index will be calculated. Participants will be randomized to treatment group order after providing written consent. The order of active TENS, placebo TENS and no TENS will be randomized via the website (randomization.com). Simple randomization results will be concealed in sealed opaque envelopes with consecutive numbers and will not be available to the outcomes assessor. The envelopes will be signed, dated, and opened by the TENS allocator before the TENS application and after the outcomes assessor has left the room.

An overview of the study procedures is shown in Fig. 1.

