## Assignment of interventions: blinding

### Who will be blinded {17a}

Both the evaluator and data analysts will be blinded to the randomization and intervention processes. The participants and the researcher responsible for the treatment cannot be blinded due to the nature of the interventions.

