### Plans to promote participant retention and complete follow-up {18b}

The researchers will be in weekly contact with the study participants. Twenty-four hours before treatment sessions, a researcher will send text messages to remind participants of the treatment date and time. This procedure will ensure that participants receive the necessary attention and will assist in fully accompanying them during the research. If any participant fails to attend the appointment, the researchers will immediately call to inquire about the reasons for the no-show. If participants abandon the trial, the reasons will be recorded, the most recent data will be compiled, and analysis will be performed using the intention-to-treat principle.

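### Two sections give different times for opening the allocation envelope, and one envelope holding the whole order reveals later treatments before their baselines

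*Protocol article*

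**What the plan says.** All references are to the protocol article.

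- **What is randomized.** Participant timeline {13}: "Participants will be randomized to treatment group order after providing written consent". The abstract's Methods/design paragraph: "A total of 34 participants will receive all three treatments: active TENS, placebo TENS, and no treatment control".
- **What the envelopes hold.** Concealment mechanism {16b}: "Concealment of the treatment order will be achieved using sequential numbering in sealed opaque envelopes".
- **When they are opened, first statement.** Participant timeline {13}: "opened by the TENS allocator before the TENS application and after the outcomes assessor has left the room".
- **When they are opened, second statement.** Concealment mechanism {16b}: they will "only be opened before the first session by the researcher responsible for the application of the TENS treatments".
- **Where baseline falls.** Active TENS: "TENS will be placed for 30 min after baseline testing and then remain on for the post-assessment tests".
- **Who is blinded.** Who will be blinded {17a} lists the evaluator and the data analysts as blinded, and adds: "The participants and the researcher responsible for the treatment cannot be blinded due to the nature of the interventions".

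**The concern.** The article states two times for the same act. A treating researcher who follows {16b} as most readers would take it opens the envelope ahead of visit 1 and learns the whole order before any baseline is taken. One who follows {13} opens it during a visit, once baseline testing is over.

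The difference matters because the primary outcome is a pain rating that participants give themselves, before and after treatment at each visit. If the person who will apply the treatment knows what is coming, a remark or a change of manner before baseline could shift that rating differently by treatment. The same knowledge could colour decisions to defer or rebook a visit. Blinding the evaluator does not by itself close this route, since the rating comes from the participant.

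**Working it through.** The protocol gives no figure to reproduce here. The check compares the texts and then counts what the treating researcher can know at each baseline.

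**Step 1: place the two opening times on the visit timeline.** Under Active TENS, TENS goes on after baseline testing. In {13}, the envelope is opened before TENS is applied and once the assessor is out of the room. So under {13} the order of events is baseline, assessor leaves, envelope opened, treatment.

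**Step 2: decide what a session is in {16b}.**
- *Visit.* Strategies to improve adherence {11c} puts scheduled sessions on an appointment card, and {18b} sends reminders 24 hours ahead of treatment sessions. This is the ordinary reading. Opening ahead of the first session then precedes the first baseline and conflicts with {13}.
- *Treatment period.* The Sit-to-stand test section places its testing on either side of the treatment session. On this reading the opening in {16b} can fall after the first baseline, and the clash with {13} at visit 1 disappears.

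**Step 3: count the orders.** Each participant receives 3 treatments once each, so there are 3! = 6 possible orders. Assume that these are equally likely, that one researcher treats a participant at all three visits, and that this researcher remembers earlier treatments. With k treatments already known, the chance of correctly naming the next one is 1/(3 − k), and it is 1 once the order has been seen.

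| Rule | Baseline 1 | Baseline 2 | Baseline 3 | Mean |
|---|---|---|---|---|
| {16b}, session = visit, whole order opened first | 1 | 1 | 1 | 1.00 |
| {13}, or {16b} with session = treatment period; one envelope with the whole order | 1/3 | 1 | 1 | (1/3 + 1 + 1)/3 = 0.78 |
| One envelope per session, opened after that day's baseline | 1/3 | 1/2 | 1 | (1/3 + 1/2 + 1)/3 = 0.61 |

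**Step 4: turn this into baselines.** With 34 participants and full attendance there are 34 × 3 = 102 baselines. Those taken while the treating researcher does not know the coming treatment for certain number 0, 34 and 34 × 2 = 68 under the three rules. Of the 68, the 34 first baselines are fully concealed (1/3 is pure chance among three treatments). The 34 second baselines are only partly concealed (1/2).

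Two things follow. Adopting {13} unchanged still exposes visits 2 and 3 if one envelope holds the order, and the article does not say whether envelopes are per participant or per visit. No envelope scheme can protect visit 3 when each treatment is given exactly once.

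**The case against.** The strongest reply has four parts.

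1. *The two sections may agree.* If a session means the treatment period, both describe an opening after the first baseline. This reading is available, though less natural given {11c} and {18b}. It removes the clash at visit 1 only. With one envelope for the whole order, treatments 2 and 3 are still known ahead of their baselines.

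2. *The people who test and contact participants are blinded.* Outcomes are collected by an evaluator who is blinded under {17a}, and {11c} gives the weekly contact to an evaluator. A reader might infer from "The researchers will be in weekly contact with the study participants" in {18b} that the treating researcher is in touch between visits and so influences attendance. The text does not say which researchers these are, so that inference is not supported. Nor does any section place the treating researcher at baseline testing. This part of the objection stands: harm requires that researcher to disclose or act on the assignment.

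3. *Participants may be blind where it matters.* {17a} says participants cannot be blinded, but the Placebo TENS section intends the recipient not to know whether the device is active. It would be selective to rest the point on {17a} alone.

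4. *The usual purpose of concealment is served.* Randomization follows consent, an independent researcher performs it, the envelopes are kept in a secure cabinet, and everyone is due all three treatments. Selection at enrolment is not at issue. This also stands, and it limits the weight of the point.

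**Conclusion.** The point holds as an inconsistency with an avoidable exposure, not as a finding of biased results. On the ordinary reading, {13} and {16b} cannot both be followed, and {16b} leaves none of the 102 baselines concealed from the treating researcher. On the narrower reading, 34 of 102 are concealed. One envelope per session would raise this to 68 of 102, half of them only partly concealed. These counts rest on six equally likely orders, full attendance and one treating researcher per participant.

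A reader might go further and conclude that the active versus placebo and active versus no-treatment contrasts are biased. The documents do not support that, because they describe no leakage. Nor can the effect be sized from them. If foreknowledge moved one condition's baseline NPRS by 0.25 to 0.5 points, an unadjusted change score would move by 0.25/2 = 12.5% to 0.5/2 = 25% of the 2-point difference in Sample size {14}. But that shift is purely assumed. The calculation also supposes no matching shift in the post-treatment rating, and the article does not specify an unadjusted change-score analysis.

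The point is worth acting on because the remedy is cheap and the outcome is self-rated.

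**What to change.** Reconcile Participant timeline {13} and Concealment mechanism {16b} to a single rule:

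- The independent researcher prepares one sealed, opaque, numbered envelope per participant per session, each holding only that session's treatment.
- The treating researcher opens, signs and dates it only once that day's baseline testing is finished and the assessor has left.
- In {16b}, delete the wording that ties opening to the time ahead of the first session.
- For participants already treated, record which opening rule was followed.

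The cost is 34 × 3 = 102 envelopes in place of 34 (taking the present scheme as one per participant), slightly more handling, and a short wait before device set-up. The amendment must go to the IRB under the section on communicating amendments {25}. The article appeared in April 2024, inside the planned recruitment window of August 2023 to August 2024, so the procedure may differ between earlier and later participants. That is why the record is needed. No extra participants, visits or staff are required.

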### Implementation {16c}

An independent researcher with no other role in this study will perform the randomization.

## Assignment of interventions: blinding

### Who will be blinded {17a}

Both the evaluator and data analysts will be blinded to the randomization and intervention processes. The participants and the researcher responsible for the treatment cannot be blinded due to the nature of the interventions.

### Procedure for unblinding if needed {17b}

The outcome evaluator and data analysts will not be allowed to unblock the blinding. However, the researcher responsible for applying the treatments will not be blinded.

## Data collection and management

### Plans for assessment and collection of outcomes {18a}

All researchers, including the person responsible for the interventions and the outcome evaluator, will undergo training before the experiment. Intra-examiner reliability will be estimated for the pressure pain threshold and temporal summation measurements by calculation of intraclass correlation coefficient (ICC). All data will be anonymized and stored in a folder on the institutional One Drive cloud. Only the study team will have access to this study folder.

### Plans to promote participant retention and complete follow-up {18b}

The researchers will be in weekly contact with the study participants. Twenty-four hours before treatment sessions, a researcher will send text messages to remind participants of the treatment date and time. This procedure will ensure that participants receive the necessary attention and will assist in fully accompanying them during the research. If any participant fails to attend the appointment, the researchers will immediately call to inquire about the reasons for the no-show. If participants abandon the trial, the reasons will be recorded, the most recent data will be compiled, and analysis will be performed using the intention-to-treat principle.

### Data management {19}

All the data will be collected weekly and stored on a secure computer server, with personal login access authorized by the principal investigator of the present study. All data collected in this trial will be restricted to the principal investigator and specific research team members.

### Confidentiality {27}

The information collected will remain anonymous; participants will be assigned a participant number for identification purposes. The data will be stored on the institutional One Drive of the University of Hartford which only the research team can access.

### Plans for collection, laboratory evaluation, and storage of biological specimens for genetic or molecular analysis in this trial/future use {33}

N/A. No biological specimens will be collected as part of this trial.

## Statistical methods

### Statistical methods for primary and secondary outcomes {20a}

An assessor blinded to the randomization and assessment processes will perform the data analysis for the primary and secondary outcomes. The intention-to-treat principle will be adopted in the analyses. Descriptive statistics (mean, standard deviation, 95% confidence intervals) will be generated for all variables. Normality will be evaluated using the Kolmogorov–Smirnov test and the Levene’s test will be used to assess for homogeneity of variance. Repeated measures ANOVA and the Tukey test will be used for normally distributed data. The Friedman test, followed by post hoc pairwise comparisons using the Wilcoxon Signed Ranks test, will be used if data are not normally distributed. Cohen’s d test will be used to calculate the effect size for normally distributed data and it was classified as small (0.0–0.2), moderate (0.3–0.5), or large (≥ 0.6) [33]. For non-normally distributed data the effect size will be calculated by the Cliff’s delta classified as small (0.147 ≤ 0.330), medium (0.330 ≤ 0.474), or large (≥ 0.474) [34]. These analyses will be performed using the SPSS v.28 statistical software (SPSS, Inc., IL, USA). Statistical significance will be considered at *p* <  0.05.

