### Outcomes {12}

The primary outcome will be pain intensity at rest and with movement, determined using the NPRS. The secondary outcomes will be pressure pain threshold (PPT), heat pain threshold (HPT), temporal summation (TS) of pain, conditioned pain modulation (CPM), sit-to-stand test, and repeated trunk flexion. CPM will be used to assess descending inhibition. Sit-to-stand and repeated trunk flexion will be used to assess function. These outcomes will be measured twice, once as a baseline testing, and then again post-treatment.

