#### Numeric pain rating scale (NPRS)

Resting pain intensity and pain with movement (during the sit-to-stand and repeated flexion tests) at the lumbar spine will be assessed before and after intervention (primary outcome measures). We will be using an 11 point NPRS for pain intensity measurements. Pain scores range from 0 representing “no pain” and 10 representing the “worst pain imaginable” [20].

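### A Kolmogorov-Smirnov pretest on an 11-point integer scale chooses the primary test and effect measure, and the variance check named beside it (Levene) does not fit a crossover

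*Protocol article*

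**What the plan says.** All points are in the protocol article.

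- **Primary outcome** (Outcomes {12}): "The primary outcome will be pain intensity at rest and with movement, determined using the NPRS". The scale is discrete (Numeric pain rating scale): "We will be using an 11 point NPRS for pain intensity measurements". Each session gives a baseline and a post-treatment value: "These outcomes will be measured twice, once as a baseline testing, and then again post-treatment".
- **Design** (abstract, Methods/design): the same 34 people receive active TENS, placebo TENS and no treatment.
- **Assumption checks** (Statistical methods {20a}): normality is judged by Kolmogorov-Smirnov, and "the Levene’s test will be used to assess for homogeneity of variance".
- **Route if normal** (same section): "Repeated measures ANOVA and the Tukey test will be used for normally distributed data".
- **Route if not normal** (same section): "The Friedman test, followed by post hoc pairwise comparisons using the Wilcoxon Signed Ranks test, will be used if data are not normally distributed".
- **Effect measure** (same section): it switches with the route, from Cohen's d to Cliff's delta.
- **Software** (same section): "These analyses will be performed using the SPSS v.28 statistical software". The K-S version is not named.
- **Planning values** (Sample size {14}): a 2-point difference, SD 1.9, 15% loss, N = 34.

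**The concern.** Two methods are fixed badly on the page.

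First, the primary test is chosen by the trial data through a test that assumes a continuous variable. Integer pain scores pile up on a few values, so a normality test can reject because of that coarseness. This says little about whether a comparison of mean differences is sound with about 30 people. The result also changes what is reported. The two primary pain measures could end up with different tests and different effect measures. The rank route names no between-treatment mean difference to compare with the 2-point criterion of the sample size section.

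Second, Levene's test compares the spread of independent groups. Here the three conditions come from the same participants, and the section names no between-participant factor to which Levene could apply. What the stated ANOVA needs is sphericity, meaning equal variances of the pairwise differences between conditions. Levene does not look at differences or correlations.

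**Working it through.** The plan attaches no figure to its testing rule, so there is none to reproduce. From the documents: SD 1.9, N = 34, loss 15%, scale 0 to 10. Evaluable n = 34 × 0.85 = 28.9, taken as 29. The means, the alternative SD of 1.5 and all correlations are assumptions.

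**Step 1. Why rounding matters.** Take normal pain with mean 5 and SD 1.9, rounded to integers. The cumulative share at score 5 is Φ(0.5/1.9) = 0.604, where the fitted normal curve gives 0.500. The built-in gap is about 0.104 before any sampling error. The simulated 5% critical values for the K-S distance are:

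| n | Lilliefors (mean and SD estimated) | Plain K-S |
|---|---|---|
| 29 | 0.162 | 0.246 |
| 34 | 0.150 | 0.227 |

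The gap uses up most of the Lilliefors margin and less than half of the plain one.

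**Step 2. Rejection rates for truly normal pain, means 3 to 5.**

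| | Lilliefors, unrounded | Lilliefors, integers | Plain K-S, integers |
|---|---|---|---|
| SD 1.9, n = 29 | 5% | 49–52% | 1.4–1.6% |
| SD 1.9, n = 34 | 5% | 59–63% | 2.1–2.2% |
| SD 1.5, n = 29 | 5% | 72–73% | about 4.5% |
| SD 1.5, n = 34 | 5% | 83% | about 7% |

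Integer change scores behave alike (50% and 60% at SD 1.9 for n = 29 and 34). If each condition is tested separately (SD 1.9; means 3, 4.5 and 5; correlation 0.5 or 0.7), at least one of three fails in 86–94% of trials with Lilliefors and in 4–7% with plain K-S. Unrounded scores under Lilliefors give 14%. The plain test hardly ever rejects unrounded normal data (about 0.01%), so it is not a calibrated check either.

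**Step 3. Levene on three within-person conditions** (n = 34, 20,000 simulations).

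| SDs (active, placebo, none) | Correlations: with active / placebo–none | Epsilon | Levene rejects | Mauchly rejects | Unadjusted F, type I error | Greenhouse-Geisser |
|---|---|---|---|---|---|---|
| 1.9, 1.9, 1.9 | 0.5 / 0.5 | 1.00 | 2.3% | 5.0% | 5.0% | 4.6% |
| 1.9, 1.9, 1.9 | 0.8 / 0.8 | 1.00 | 0.2% | 4.8% | 5.3% | 5.0% |
| 1.9, 1.9, 1.9 | 0.4 / 0.8 | 0.75 | 2.4% | 92% | 6.3% | 4.8% |
| 1.9, 1.9, 1.9 | 0.3 / 0.9 | 0.61 | 3.2% | >99% | 7.5% | 5.1% |
| 2.4, 1.9, 1.9 | 0.4 / 0.8 | 0.69 | 21% | 99% | 6.9% | 5.0% |

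With equal variances Levene misses its nominal 5%. When only the correlations differ it sees almost nothing. When the SDs differ too, it reacts in about a fifth of trials.

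**Step 4. What non-sphericity would do to a pooled error term** (illustration: SDs 2.4, 1.9, 1.9; correlations 0.3 with active, 0.8 otherwise; n = 29).

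- Var(active − placebo) = 2.4² + 1.9² − 2(0.3)(2.4)(1.9) = 6.63. Active minus none is the same.
- Var(placebo − none) = 2(1.9²)(1 − 0.8) = 1.44.
- Pooled value = (6.63 + 6.63 + 1.44)/3 = 4.90.
- Ratios: 6.63/4.90 = 1.35 and 1.44/4.90 = 0.29. The pooled SE for active versus placebo is 1/√1.35 = 0.86 of the true one.
- Type I error of the unadjusted F is about 7%, and 5% with Greenhouse-Geisser.

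**Step 5. Does the route change the answer?** Integer scores, SD 1.9, n = 29, correlation 0.3 to 0.5.

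| True effect of active TENS | ANOVA power | Friedman power | Verdicts differ |
|---|---|---|---|
| 2 points | >0.99 | >0.99 | 0.1–0.5% |
| 1 point | 0.65–0.80 | 0.55–0.71 | 13–17% |

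At no effect both routes reject about 5% of the time.

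**The case against.** The rule is written in advance and the analyst is blinded, so the switch is not discretionary. At the planned effect either route would succeed. Both facts stand and limit the severity.

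Several stronger readings are tempting, but the documents do not support them:

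- **That Levene helps choose the test.** The switch is worded on normality alone, and no consequence is attached to Levene's result.
- **That sphericity will go uncorrected.** The article is silent, but an analysis plan that is not shown may add a correction. The Tukey error term is not stated either, so the pooled-error arithmetic is an illustration with assumed SDs and correlations. The error on the page is that Levene is named.
- **That rounding decides the route whatever K-S test is run.** This holds for the Lilliefors form only. Rates at means near 2 are higher still, but part of that is a real floor effect, so only means 3 to 5 are used here. The calculation also takes single integer ratings. If movement ratings were averaged to half points, the gap in Step 1 would fall to Φ(0.25/1.9) − 0.5 = 0.052 and the effect would shrink.
- **That the rank route uniquely drops people who miss a session.** Conventional repeated measures ANOVA also needs complete cases. The sections on discontinuation {11b} and retention {18b} say recent data will be used, and the missing-data section {20c} cites a guideline.
- **That the rank route reports no means or intervals at all.** Means, SDs and 95% CIs are promised for every variable. They are descriptive, however, and not stated to be intervals for treatment differences.

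**Conclusion.** The point holds in a limited form. The protocol hands the choice of primary test and effect measure to a K-S pretest on an 11-point integer scale. That choice swings from about 2% to about 50–63% rank analyses for the same normal pain scores (SD 1.9, means 3 to 5, n = 29 to 34), depending on a test version it does not name. Naming the version later would not repair the rule: one version reacts to rounding and the other hardly reacts at all. Levene's test is a wrong method for three conditions in the same people, although it has no stated effect on the route. Consequences are moderate: negligible at a 2-point effect, and disagreement in 13–17% of simulated trials at 1 point under correlations of 0.3 to 0.5. The inflation to about 7% in the unadjusted ANOVA rests wholly on assumed covariances and on no correction being made. The change should be made, but the trial's validity does not hang on it.

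**What to change.** In Statistical methods {20a}, delete the K-S switch and Levene's test. Fix one primary analysis in advance for the NPRS outcomes, by either of two routes:

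- a linear mixed model with unstructured within-participant covariance and small-sample degrees of freedom; or
- repeated measures ANOVA with a Greenhouse-Geisser correction and Holm-adjusted paired contrasts in place of Tukey.

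Report between-treatment mean differences with 95% CIs for both rest pain and movement pain, so that each can be compared with the 2-point criterion. Keep Friedman and Wilcoxon as a sensitivity analysis, reported whatever the primary result. Either choice answers the point. The cost is wording only: no extra participants, visits or measurements. It should be settled before the data are unblinded to the analyst.
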